## Abstract

**Background:**

Penile cancer is a rare male genital malignancy. Surgical excision of the primary tumour is followed by radical inguinal lymphadenectomy if there is metastatic disease detected by biopsy, fine needle aspiration cytology (FNAC) or following sentinel lymph node biopsy in patients with impalpable disease. However, radical inguinal lymphadenectomy is associated with a high morbidity rate, and there is increasing usage of a videoendoscopic approach as an alternative.

**Methods:**

A pragmatic, UK-wide multicentre feasibility randomised controlled trial (RCT), comparing videoendoscopic radical inguinal lymphadenectomy versus open radical inguinal lymphadenectomy. Patients will be identified and recruited from supraregional multi-disciplinary team meetings (sMDT) and must be aged 18 or over requiring inguinal lymphadenectomy, with no contraindications to surgical intervention for their cancer. Participants will be followed up for 6 months following randomisation. The primary outcome is the ability to recruit patients for randomisation across all selected sites and the rate of loss to follow-up. Other outcomes include acceptability of the trial and intervention to patients and healthcare professionals assessed by qualitative research and obtaining resource utilisation information for health economic analysis.

**Discussion:**

There are currently no other published RCTs comparing videoendoscopic versus open radical inguinal lymphadenectomy. Ongoing study is required to determine whether randomising patients to either procedure is feasible and acceptable to patients. The results of this study may determine the design of a subsequent trial.

**Trial registration:**

Clinicaltrials.gov PRS registry, registration number NCT05592639. Date of registration: 13th October 2022, retrospectively registered

**Supplementary Information:**

The online version contains supplementary material available at 10.1186/s40814-024-01474-8.

## Background

Penile cancer (PeCa) is a rare male genital malignancy. A total of 637 cases of penile cancer were recorded in the UK in 2015 with approximately 134 deaths in 2016 [1]. However, the incidence of PeCa in Western countries is increasing [2–4]. Squamous cell carcinoma is the most common histological subtype and accounts for more than 90% of penile cancers [3, 4]. Other cancers of the penis include mucosal melanoma and sarcoma [3].

The surgical management depends on the stage of the disease [5]. Localised tumour can undergo penile preserving surgery (PPS) which includes glans resurfacing (PeIN, T1), glansectomy (T2), and partial penectomy (T3). Total penectomy is a non-organ preserving procedure, reserved for locally advanced PeCa [6].

The presence of metastatic disease in the inguinal lymph nodes is one of the most important prognostic indicators in PeCa [7, 8]. Up to 25% of PeCa patients with impalpable inguinal lymph nodes may harbour micrometastatic disease [8]. The sensitivity of CT, MRI, and ultrasound-guided fine needle aspiration (FNAC) is suboptimal to detect micrometastases [6, 8]. Therefore, dynamic sentinel lymph node biopsy (DSLNB) or superficial modified inguinal lymphadenectomy with frozen section analysis are the main treatment options for lymph node management in patients with impalpable inguinal lymph nodes. High risk tumours include tumour stage >T1b (tumour exhibits lymphovascular invasion and/or perineural invasion or is high grade, i.e. grade 2/3 or sarcomatoid subtype) [6, 8]. If there is metastatic disease in the sentinel lymph node, radical inguinal lymphadenectomy is recommended, as this has been shown to improve cancer-specific survival [6, 8]. Open inguinal lymphadenectomy is an option if DSLNB is unavailable or unable to be performed; for example in patients who have undergone a total penectomy, have non-visualisation on dynamic sentinel node imaging or if nuclear medicine facilities are unavailable. Surveillance may be applicable in selected patients with T1a disease or less with clinically impalpable inguinal nodes. In men with PeCa and palpable inguinal nodes, FNAC or open biopsy followed by radical inguinal lymphadenectomy is the recommended treatment [6, 8].

### Aims

The aim of the study is to assess the feasibility of performing a RCT comparing videoendoscopic inguinal lymphadenectomy versus open radical inguinal lymphadenectomy in men with penile or urethral cancer requiring inguinal lymphadenectomy, and determine the design of a definitive RCT.

## Rationale

### Justification for a randomised controlled trial

It is important to evaluate the effectiveness and cost-effectiveness of VEIL versus open radical inguinal lymphadenectomy in men with PeCa. The effectiveness from observational studies may be influenced by selection bias, i.e. people with smaller and mobile nodes would have been chosen for VEIL, while those with large and fixed nodes would have been chosen for open lymphadenectomy. RCTs overcome this risk of selection bias. The lack of major completed or ongoing trials shows that well-designed studies are necessary.

### Justification for a feasibility study

In the only previously attempted RCT which compared VEIL versus open inguinal lymphadenectomy for multiple cancers (but mainly melanomas), randomisation could not be performed because of patient preference [9]. This was despite the absence of information on long-term oncologic outcomes and increased incidence of lymphocele in patients undergoing VEIL versus open inguinal lymphadenectomy for PeCa. The primary outcome in that RCT was wound complications [9]. However, our survey in the PeCa patient support group indicated that people rated complications differently, suggesting that some complications are more important than others. Therefore, it is important to judge the acceptability of the trial to patients and clinicians, the acceptance of randomisation, estimate the recruitment rate, informing the primary outcome of a definitive trial, and the difference in the primary outcome that can be considered clinically meaningful. A feasibility study is therefore necessary to assist in the design of a definitive RCT.

## Methods

### Study design

This is a pragmatic, UK-wide multicentre feasibility RCT, involving four NHS Foundation Trusts (University College London Hospitals, The Christie Hospital, Norfolk and Norwich University Hospitals, St George’s University Hospitals).

Patients requiring inguinal lymphadenectomy who fulfil the inclusion/exclusion criteria (see Table 1) will be identified during the sMDT meetings and in outpatient clinics.

**Table 1 Tab1:** Inclusion and exclusion criteria

Inclusion criteria	1. Patients requiring inguinal lymphadenectomy
	a) Patients with squamous cell carcinoma or mucosal melanoma of the penis > T1bG2 or patients with urethral cancer requiring inguinal lymphadenectomy
	b) Patients unsuitable for dynamic sentinel node biopsy (DSNB) with impalpable nodes (previous penectomy or non-visualisation at previous DSNB)
	c) Previous DSNB with metastatic inguinal nodes on histology or FNA-positive nodes on cytology who require a completion radical inguinal lymphadenectomy
	d) Small volume palpable inguinal lymph nodes (< 2 cm on CT) not fixed to skin
	2. Aged > 18 years
Exclusion criteria	1. Unfit for surgery
	2. People unlikely to benefit from lymphadenectomy because of advanced cancer
	3. Those with palpable inguinal lymph nodes fixed to skin or adjacent structures
	4. Does not want to participate in the trial or unable to provide informed consent

### Trial outcomes

The aim is to assess the feasibility of performing a RCT comparing videoendoscopic inguinal lymphadenectomy versus open radical inguinal lymphadenectomy in men with penile or urethral cancer requiring inguinal lymphadenectomy, and determine the design of a definitive RCT.

The primary outcome for this trial will be the feasibility of the RCT as assessed by:Ability to recruit patients across all participating sites (recruitment rate). We aim to recruit (randomise) > 30% (0.3) of eligible patients approached.Acceptability of the trial design and intervention to both patients and healthcare professionals through semi-structured interviews.

Recruitment rate will be monitored through screening and randomisation logs with the aim to recruit approximately three patients per month at all four sites.

There is currently no core outcome set for trials on patients with PeCa. Patient representatives and clinicians have identified complete removal of the cancer, different types of complications, successful completion of VEIL without requiring conversion to open lymphadenectomy, overall survival, health-related quality of life, length of hospital stay, return to normal activity, and the number of workdays lost (in those who work) as important outcome measures. These will be considered in this feasibility trial to help in the design of a definitive trial. We will measure these outcomes at 6 months after surgery.

### Randomisation and blinding

Randomisation will be performed using a web-based platform via pre-prepared lists from the Trial Statistician with stratification by the centre and stage of cancer (I or II) and a block size of 2 or 4. The randomisation schedule will be concealed from all members of the clinical teams.

It is not possible to blind the healthcare providers or patients to the treatment received. Blinding of patients is not possible post-operatively. We do not anticipate any outcome measured within this period as the primary outcome of the trial. We will attempt to blind the outcome assessors of the long-term complications and oncologic outcomes. Lack of blinding will not result in a bias of the primary outcomes of the trial, namely assessment of feasibility of a definitive RCT as assessed by ability to recruit patients at the selected sites (recruitment rate) and acceptability of the trial/intervention to patients and healthcare professionals.

### Intervention

The trial compares videoendoscopic radical inguinal lymphadenectomy (intervention) versus open radical inguinal lymphadenectomy (control).

Surgical technique is based on individual surgeons; however all centres involved in the trial carry out high-volume penile cancer surgery, including inguinal lymph node dissection. Multiple techniques exist for open inguinal lymphadenectomy, although all techniques remove the inguinal lymph nodes in both the superficial and inguinal group.

### Consenting

In a previous RCT comparing VEIL and open inguinal lymphadenectomy for melanoma in the USA, there was patient preference for VEIL. Given VEIL in the treatment of PeCa is established but not yet standard in the UK, we do not anticipate patient preference for VEIL. Should the participant indicate preference for either intervention at approach, we will offer randomisation and reiterate that the outcome represents the intention to treat with that intervention.

Information about the trial is given to patients face-to-face and in the form of a patient information leaflet. Only clinical staff trained in research delivery as evidenced by completion of Good Clinical Practice training will approach potential participants. Patient information leaflets have been reviewed and approved by the chief investigator, the trial team and the oversight committee. Patients are then given a minimum of 24 h to comprehend the information, with opportunity given for clarification, before deciding whether to participate in the RCT.

### Follow-up and timing of measurement of outcomes

Participants will be followed up for 6 months from randomisation. Outcomes will be measured at randomisation, 1 week, 3 to 4 weeks, 3 months, and 6 months (see Fig. 1 and Table 2).

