**Fig. 1 Fig1:**
[figure not shown]
Participant flow chart

**Table 2 Tab2:** Assessment and visit schedule (SPIRIT figure)

Time point	Pre-intervention		Intervention phase	Follow up phase			
Assessments	Screening	Baseline		1 week	3–4 weeks	3 months	6 months
Inclusion and exclusion criteria	X						
Consent	X						
Registration		X					
Randomisation	X						
Demographic data		X					
Medical history		X					
Concomitant medications		X					
Tumour characteristics (including stage)		X					
CT scan						X	X
Outcome data				X	X	X	X
AE reporting			X	X	X	X	X

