## Statistical analysis

### Quantitative analysis

Since this is a feasibility study, all analyses other than recruitment rate should be considered exploratory. Acceptability of the trial design to both patients and healthcare professionals will be assessed. Any exploratory comparisons will use means and standard deviations or medians and inter-quartile ranges for continuous variables, as appropriate, and frequency counts and percentages for categorical variables. The proportion of patients who consent to be randomised will be presented with a 95% confidence interval. For other outcomes, we will explore the mean difference in proportion (for binary outcomes) and mean or median difference (continuous outcomes) between the two groups and will be presented with associated 95% confidence intervals. No pre-specified formal comparisons between the groups will be made and no hypothesis tests will be carried out.

Other outcomes which may be considered are complete removal of the cancer, different types of complications, successful completion of VEIL without requiring conversion to open lymphadenectomy, overall survival, health-related quality of life, length of hospital stay, return to normal activity, and the number of workdays lost (in those who work). The randomisation stratification factors of centre and stage of cancer will be considered adjusting factors where appropriate. The results will inform us how sensitive the outcome measures are and, along with other information, will be used to determine the primary outcome of a subsequent large RCT. These results will inform the calculations for a sample size calculation for the most appropriate primary outcome. Any missing data mechanisms will be summarised from the VELRAD trial in preparation for a follow-on trial.

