### Health economic analysis

We will undertake a feasibility study for an economic evaluation to compare VEIL with open inguinal lymphadenectomy in men with penile or urethral cancer. The feasibility study will be used to plan the evaluation within a subsequent trial, which will aim to estimate the incremental cost of the VEIL and the potential benefit in economic terms from the NHS perspective and personal social services (PSS) perspective versus open inguinal radical lymphadenectomy in men with penile or urethral cancer. We will also explore the feasibility of collecting data to assess the costs for patients and families from a broader perspective.

With the available data, we will perform a preliminary analysis of the cost-utility of VEIL with open inguinal lymphadenectomy in men with penile or urethral cancer to inform a future trial.

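### The follow-up section measures outcomes at randomisation but Table 2 starts at 1 week, so it is unsettled whether quality of life and utility have a pre-surgery value

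*Protocol article*

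**What the plan says.** All references are to the protocol article. It times its outcomes in three places.

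- **Follow-up and timing of measurement of outcomes:** "Outcomes will be measured at randomisation, 1 week, 3 to 4 weeks, 3 months, and 6 months". The sentence refers the reader to Fig. 1 and Table 2.
- **Table 2 (assessment and visit schedule):** one pooled row, "Outcome data X X X X", whose four marks fall at 1 week, 3–4 weeks, 3 months and 6 months. The Screening, Baseline and intervention cells of that row are empty.
- **Trial outcomes:** after a list that includes health-related quality of life, return to normal activity and workdays lost, it says "We will measure these outcomes at 6 months after surgery".

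Two analysis sections depend on this timing. Under Health economic analysis, "we will perform a preliminary analysis of the cost-utility of VEIL with open inguinal lymphadenectomy". Under Quantitative analysis, "The randomisation stratification factors of centre and stage of cancer will be considered adjusting factors where appropriate". That section also says the results will feed the choice of primary outcome and the sample size of the definitive trial.

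**The concern.** The text gives five measurement times and the table it cites gives four. The one that differs is the only one before surgery. A pre-surgery quality-of-life or utility value cannot be collected afterwards, so a site that works from the table loses it for good.

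Three things would be affected. QALYs counted from randomisation would have no starting utility. The exploratory quality-of-life difference could not be adjusted for a chance imbalance at entry. The SD passed on to the definitive trial could only be the unadjusted one, with no estimate of the correlation between baseline and follow-up. Return to normal activity and workdays lost also need a record of usual activity and employment status before surgery.

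**Working it through.** **1. The plan's own figure.** The Sample size justification gives ±7% for a 30% recruitment rate among 170 patients approached. The Wald half-width is 1.96 × √(0.3 × 0.7 / 170) = 0.0689, which rounds to ±7%. The figure is reproduced, and it uses no outcome data collected after recruitment, so the timing question does not touch it.

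**2. The three statements side by side.**

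| Time | Follow-up section | Table 2, outcome row | Trial outcomes |
|---|---|---|---|
| Randomisation / baseline | yes | not marked | not mentioned |
| 1 week | yes | marked | not mentioned |
| 3–4 weeks | yes | marked | not mentioned |
| 3 months | yes | marked | not mentioned |
| 6 months | yes | marked | yes, counted from surgery |

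The follow-up section counts its 6 months from randomisation, so the time origin differs as well.

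**3. Is the empty baseline cell a fault of text extraction?** The alignment of the table argues against it. Adverse event reporting starts one column before outcome data, in the intervention phase. Demographic data fall under Baseline and CT scans under 3 and 6 months. The Baseline column holds registration, demographics, medical history, concomitant medications and tumour characteristics, and no quality-of-life or utility item. Randomisation is marked under Screening, one column ahead of Baseline.

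**4. What a missing baseline would cost in QALYs, if Table 2 governs.** Assumptions, none of them given in the article: trapezoidal QALYs over 26 weeks from randomisation; visits at 1, 3.5 and 13 weeks counted from surgery; last visit at 26 weeks from randomisation; surgery *g* weeks after randomisation.

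- Share of follow-up before the first utility = (g + 1) / 26.
- Weight of the baseline utility in the QALY = half of that, (g + 1) / 52.

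| g (weeks) | Before first utility | Baseline weight |
|---|---|---|
| 0 | 1/26 = 4% | 1/52 = 2% |
| 2 | 3/26 = 12% | 3/52 = 6% |
| 4 | 5/26 = 19% | 5/52 = 10% |
| 6 | 7/26 = 27% | 7/52 = 13% |

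**5. What losing baseline adjustment would cost.** For a baseline-to-follow-up correlation r, adjustment multiplies the residual variance by 1 − r². The article gives no r, so a range is assumed:

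- r = 0.3: 1 − 0.09 = 0.91
- r = 0.5: 1 − 0.25 = 0.75
- r = 0.7: 1 − 0.49 = 0.51

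**6. How large a chance imbalance could be.** With up to 50 randomised 1:1, about 25 per arm, the standard error of the baseline difference between arms is √(1/25 + 1/25) = 0.28 SD. Without a baseline value, an imbalance of that order could be neither seen nor adjusted for.

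**The case against.** The strongest reply is that the mismatch proves little about quality of life. Table 2 has a single pooled row for all outcomes. Most of those outcomes cannot exist before surgery: complete removal, complications, conversion, length of stay. An empty baseline cell in such a row is weak evidence that a questionnaire is omitted, and instruments and item-level schedules are normally left to the full protocol. Quality of life is only among outcomes the article may consider ("Other outcomes which may be considered are complete removal of the cancer, different types of complications"), everything except the recruitment rate is exploratory, and the cost-utility work is preliminary.

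Much of this stands, and it rules out three stronger readings that a reader might infer.

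- **That quality of life has no baseline.** This follows only if Table 2 overrides the follow-up section. Nothing in the article says so, and the follow-up section says the opposite.
- **That the analysis excludes a baseline covariate.** The Quantitative analysis section names centre and stage as factors to consider; it does not limit adjustment to them. Further covariates may properly be left to the SAP.
- **That the definitive trial would be greatly oversized.** The inverse of 1 − r² is 1/0.91 = 1.10, 1/0.75 = 1.33 and 1/0.51 = 1.96, which can be read as 10% to 96% too many patients. That holds only if r is as assumed, if quality of life becomes the primary outcome, and if a baseline-adjusted trial is sized on the unadjusted SD. The article leaves that primary outcome open, and most candidates have no baseline value.

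The reply does not remove the contradiction. The article does not merely leave the schedule out. It states schedules that cannot all be right, and the disputed point cannot be recovered later.

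**Conclusion.** The contradiction between the follow-up section, Table 2 and the Trial outcomes section is real and can be checked on the page. Its consequence is conditional. If Table 2 is followed, quality of life lacks a pre-surgery value, the preliminary cost-utility analysis lacks a starting utility, and the quality-of-life difference and its SD cannot be baseline-adjusted. If the follow-up section is followed, none of this arises.

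Under the table, the missing utility would carry about 2% of the QALY weight with no wait for surgery and 13% with an assumed 6-week wait. The forgone variance reduction is 9%, 25% or 49% for an assumed r of 0.3, 0.5 or 0.7. These figures show what is at stake; they do not estimate a loss, because neither the wait nor r is in the article. The primary feasibility outcome and its precision are unaffected.

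The point should still be settled, because the trial exists to design the next one and a lost baseline cannot be replaced.

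**What to change.** 1. Reconcile the follow-up section, Table 2 and the Trial outcomes section so that they give one set of measurement times and one time origin for the 6-month assessment.
2. Add a separate quality-of-life and utility row to Table 2, with usual activity and employment status, marked before the intervention as well as at the follow-up visits.
3. State that this set is completed after consent and before the allocation is disclosed. A mark in the Baseline column does not secure this by itself: Table 2 puts Randomisation under Screening, ahead of Baseline, and patients are not blinded. The order must be written down.
4. Use the baseline value as a covariate for the exploratory quality-of-life difference and for QALYs. Report the baseline-to-outcome correlation, and the adjusted SD beside the unadjusted one, so that the definitive trial can be sized either way.

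The cost is one questionnaire set at an existing visit and one covariate. The sample size and the primary outcome do not change.

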**Fig. 1 Fig1:**
[figure not shown]
Participant flow chart

**Table 2 Tab2:** Assessment and visit schedule (SPIRIT figure)

Time point	Pre-intervention		Intervention phase	Follow up phase			
Assessments	Screening	Baseline		1 week	3–4 weeks	3 months	6 months
Inclusion and exclusion criteria	X						
Consent	X						
Registration		X					
Randomisation	X						
Demographic data		X					
Medical history		X					
Concomitant medications		X					
Tumour characteristics (including stage)		X					
CT scan						X	X
Outcome data				X	X	X	X
AE reporting			X	X	X	X	X

